### 2.11. Data Management and Trial Monitoring

All involved investigators from different centers will be trained uniformly before the study begins, in order to maintain protocol implementation consistency. They will also be given standard operation procedures (SOPs). The electric data capture (EDC) system developed by IBRCM will be used to collect study data. This will allow for auto logical check according to preset procedures. Data managers also can send queries to investigators through the system for manual verification. Then, feedback from investigators is sent to data managers to ensure that the data can be uploaded to the system timely, accurately, and completely, so that the principal investigator can monitor research progress in real time. Data monitoring will include data traceability, recruitment, randomization, and compliance. It will be conducted regularly with SOPs by an independent department from Jilin Aodong Yanbian Pharmaceutical Co., Ltd. (Jilin, China) called the clinical data management team. Audits will be executed regularly by IBRCM at the China Academy of Chinese Medical Sciences. Meanwhile, the trial will be received the supervision and inspection of the Ministry of Science and Technology and the Hospital Scientific Research Department.

### 2.12. Ethics and Dissemination

This trial protocol has been approved by the Ethics Committee at Guangdong Provincial Hospital of Chinese Medicine (GPHCM) (Approval No. BF2019-175-01) and other ethics committees at each center. Written informed consent must be obtained from all participants. The study will be conducted in compliance with the Declaration of Helsinki [39] and good clinical practice guidelines [40]. The results will be published in a peer-reviewed journal and a PhD dissertation and will be presented at conferences.

## 3. Discussion

To our knowledge, this is the first study to investigate the efficacy and safety of XFZY for TTH, compared to a placebo treatment. Although existing pharmacological and nonpharmacological treatments have been shown to be helpful [11, 41–43], the evidence available for treatment efficacy is limited to small magnitude or adverse events. Hence, new pharmacologic treatments are expected.

Both ETTH and CTTH patients are target populations of this study. However, they are categorized differently according to ICHD-3 criteria and have variant pathogenesis [44, 45]. Yet, the two diseases can be identified by the same CM pattern and are judged by similar signs and symptoms. QBS is a common TTH pattern. XFZY is a classical formula that promotes the flow of *qi* and *blood* in CM. Hence, we will conduct a randomized, double-blinded, placebo-controlled trial to evaluate the effect of XFZY for TTH with QBS.

Patient-centered outcomes are the focus of this study. This is in contrast to previous studies which have concentrated on rapid relief and being pain-free after 2 h, as recommended by HIS [31]. VAS and EQ-5D-5L are reported by the subjects, and the former is the primary outcome for evaluating headache intensity, while the latter measures the quality of life. The long-term effect deserves more attention than the frequent occurrence of headache. Therefore, our study period includes 4 weeks of treatment and 8 weeks of follow-up, in order to observe the long-term response.

TTH has immense public health costs, both in China and around the world, owing to its high prevalence among the general population, especially with regard to indirect costs (i.e., lost work and leisure time). As such, the economic costs are increasing. Data from a cross-sectional survey has shown mean annual costs of €303 per capita for tension-type headache in Europe [46]. Among them, the direct cost is €25, less than CNY 468 per person in China [47]. In order to assess costs and cost-effectiveness for patients taking XFZY compared with patients receiving placebo, we will calculate the health economic index as one of the outcome measures.

In conclusion, the results of this study are expected to provide evidence of high methodological quality on the efficacy and safety of XFZY for TTH.

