## 1. Introduction

Tension-type headache (TTH) is the most prevalent headache disorder [1, 2] and the second most common disease in the 2010 Global Burden of Disease Survey [3, 4]. It has a lifetime prevalence ranging from 30% to 78% [5]. In China, the years lived with disability (YLDS) for TTH are second only to migraine among headache disorders [2]. This has immense social and economic costs. Overall absence rates for subjects with frequent TTH are on the rise, despite not increasing for migraines [6]. Hence, it is one of the most costly disorders to society [7]. In order to improve Chinese citizens' quality of life, treating TTH should be a national priority [2].

Simple analgesics and nonsteroidal anti-inflammatory drugs (NSAIDS) are recommended for episodic TTH (ETTH) by the European Federation of Neurological Societies (EFNS) [8] and the British Association for the Study of Headache (BASH) [9]. They have been shown to be to be effective for ETTH [10–12] but not for chronic TTH (CTTH). As headache frequency increases, so does the risk of medication overuse, especially in CTTH. The tricyclic antidepressant amitriptyline is the primary choice for the prophylactic treatment of CTTH [8]. However, the effect of these drugs is not satisfactory because of insufficient effect or side effects [13, 14]. The combination of caffeine with simple analgesics is more effective for the treatment of ETTH than simple analgesics alone, but at the cost of an increased frequency of side effects [15, 16]. Hence, combination analgesics containing caffeine are treated as the second choice for ETTH by EFNS guideline [8]. Opioids should not be used because of drug resistance, dependence, and toxicity [8]. Furthermore, the use of these drugs also increases the risk of forming medication-overuse headache (MOH) [17]. Other treatments have also been applied in clinic, including Chinese medicine (CM) therapies, cognitive behavioral therapy, physical therapy, stress management, and acupuncture, but the evidence for these treatments is limited or inconsistent [18, 19]. Therefore, more research is needed to explore new medications.

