### 2.2. Participants

We will recruit potential eligible participants via newspaper advertisements, notice boards, and outpatient visits, and also pay attention to whether the recruitment and enrollment progress reached the target sample size. Patients who meet the inclusion criteria and sign informed consent forms will enter the screening period; otherwise, they will be excluded before randomization.

Patients in each center will be diagnosed and differentiated by a senior neurologist and will be observed by a neurologist at a specialist clinic. TTH diagnostic criteria include (1) Western medicine diagnosis based on the criteria of the International Classification of Headache Diseases-3 (ICHD-3) published by the International Headache Society (IHS) in 2018 [5] and (2) pattern diagnosis according to a validated QBS diagnostic scale [29] (Table 1).

Eligibility criteria are as follows: (1) TTH must have occurred for at least 1 year, at least 2 days per month (unlimited frequency), and at least one TTH attack needs to have lasted over 4 hours; (2) a visual analogue scale (VAS) score ≥3 cm; (3) the first onset of TTH need to have happened before the age of 50 years; (4) aged 18–65 years; and (5) CM pattern differentiation is QBS.

Exclusion criteria are (1) concurrent migraine; (2) ailment diagnosed as secondary headache by computed tomography (CT) and transcranial Doppler (TCD) within the previous 6 months; (3) having serious primary diseases such as those of the cardiovascular, liver, kidney or hematopoietic system, and psychosis (schizophrenia, epilepsy, alcoholism, and anorexia) or major neuropsychiatric diseases; (4) labs showing increase in alanine aminotransferase (ALT) or aspartate aminotransferase (AST) over twice the upper limit of the normal range or an increase in creatinine over 1.5 times of the upper limit of the normal range; (5) suffering from other severe pain-inducing diseases, such as cancer; (6) patients with a Self-rating Anxiety Scale (SAS) greater than 59 or Self-rating Depression Scale (SDS) greater than 62; (7) potential allergy to XFZY; (8) women who are either pregnant, lactating, or planning to get pregnant; and (9) participating in other clinical trials within the previous month.

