### 2.3. Randomization

A block randomization sequence stratified by centers is generated by SAS 9.2 (SAS Institute Inc., Cary, USA) and performed by the Institute of Basic Research in Clinical Medicine (IBRCM), China Academy of Chinese Medical Sciences, through an interactive web response system. When eligible patients who have signed informed consent forms are enrolled, an independent researcher will log into the system to obtain their allocation results. The randomization results will be kept confidential and maintained by IBRCM. All patients and researchers, including investigators, outcome assessors, statisticians, and other staff involved in the trial will be unaware of the grouping and treatment during the study period.

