### 2.10. Statistical Analysis

The statistical analysis will be performed on the basis of a pre-established statistical analysis plan. Data analysis will be based on the intent-to-treat (ITT) and per protocol (PP) principles and will be conducted by independent qualified statisticians blinded to treatment allocation. Two-tailed *p* values less than 0.05 will be considered statistically significant. Missing data will be replaced by the multiple imputation method. All analyses will be conducted with SPSS version 18.0 (IBM SPSS Inc, Armonk, New York, USA) or SAS 9.2 (SAS Institute Inc., Cary, USA). Continuous variables will be expressed as mean ± SD if data are normally distributed. Data not normally distributed will be presented using the median and interquartile range (IQR). Categorical variables will be expressed as counts and percentages.

For primary and secondary outcomes, a full analysis set including participants with at least one treatment and outcome assessment and a perprotocol analysis set containing 4-week treatment,will be employed to compare the changes between groups with an independent *t*-test, respectively; repeated measures of analysis of variance or a liner mixed model will be applied to analyze the changes measured at different time points. Sex, age, course of disease, and center, as well as other covariates will be considered in the statistical model.

For safety assessments, a safety analysis set with all subjects who took the drug at least once will be adopted to detect whether the AE proportions are significant between the two groups. This will be performed with either a *χ*^2^ test or Fisher's exact test. All AEs will be coded based on the Chinese version of the Medical Dictionary for Regulatory Activities (MedDRA).

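### The stated t-test on VAS change uses neither baseline VAS nor headache subtype; a covariate-adjusted primary comparison would use the same data better

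*Protocol article*

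**What the plan says.** Section 3 (Discussion) states that "Both ETTH and CTTH patients are target populations of this study", that "they are categorized differently according to ICHD-3 criteria and have variant pathogenesis", and then gives the reason for treating them together: "the two diseases can be identified by the same CM pattern and are judged by similar signs and symptoms". Section 1 adds that simple analgesics and NSAIDs work in ETTH and do not work in CTTH. Section 2.2 admits anyone with two or more headache days a month, with no upper limit and no quota by subtype.

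Randomisation (section 2.3) uses "A block randomization sequence stratified by centers", with no second factor. Section 2.10 compares changes between groups with an independent t-test and analyses the repeated time points with repeated-measures ANOVA or a linear mixed model. It then says: "Sex, age, course of disease, and center, as well as other covariates will be considered in the statistical model". Baseline VAS and subtype are not named. Table 2 shows that VAS and headache frequency are both collected at week 0.

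**The concern.** A t-test on change uses the baseline only by subtraction and ignores every other predictor of outcome. The article itself singles out one clinical split, ETTH against CTTH, as different in pathogenesis and in response to simple analgesics. That makes subtype a plausible predictor of change in headache intensity, yet it is absent from the named covariates, as is baseline VAS, usually the first covariate one would want for a VAS outcome.

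Two things are at stake. One is efficiency: variance that a prognostic covariate could remove stays in the error term. The other is interpretation: if the arms differ by chance in their share of CTTH, readers will ask whether that explains part of the result, and an unadjusted comparison gives no answer.

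**Working it through.** **Inputs.** From section 2.9: mean changes 4.46 and 2.14, SD 1.5 in each arm, margin 1.7, 87 per arm, 15% loss. Evaluable patients per arm: 87 × 0.85 = 73.95, about 74. The article gives neither the CTTH share p nor the difference D between subtypes in mean VAS change. I assume p = 0.1 to 0.5 and D = 0.5 to 1.5 cm, with the total SD held at 1.5.

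**The plan's own figure.** The difference beyond the margin is 4.46 − 2.14 − 1.7 = 0.62. At the stated two-sided 5% level, n = 2 × 1.5² × (1.96 + 0.8416)² / 0.62² = 92 per arm, or 109 after dividing by 0.85. The stated 87 is not reproduced. A one-sided 5% test gives 74 (t-based), and 74/0.85 = 87.06. That discrepancy is a separate matter; here it only means that power is shown both ways.

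**Step 1: what subtype adjustment could save.** The share of variance explained by subtype is p(1 − p)D² / 1.5². The lowest case with D = 0.5 is 0.09 × 0.25 / 2.25 = 1%; the highest with D = 1.0 is 0.25 × 1.0 / 2.25 = 11%. Over p = 0.1 to 0.5:

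| D (cm) | Variance removed | SD after adjustment | Two-sided n per arm before dropout | Power, 74 per arm, two-sided | Power, one-sided |
|---|---|---|---|---|---|
| 0 | 0% | 1.50 | 92 | 0.71 | 0.81 |
| 0.5 | 1–3% | 1.48–1.49 | 90–91 | 0.72 | 0.81–0.82 |
| 1.0 | 4–11% | 1.41–1.47 | 82–89 | 0.73–0.76 | 0.82–0.85 |
| 1.5 | 9–25% | 1.30–1.43 | 69–84 | 0.75–0.83 | 0.84–0.90 |

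These figures are for subtype alone. Beside other covariates that carry the same information, its added share would be smaller.

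**Step 2: baseline VAS.** If baseline and week-12 VAS have equal variance σ² and correlation ρ, the change score has variance 2σ²(1 − ρ), while ANCOVA leaves σ²(1 − ρ²). The ratio is (1 + ρ)/2, which is below 1 for any ρ below 1. The article does not give ρ, so I put no figure on this gain.

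**Step 3: chance imbalance.** With 87 per arm and no subtype stratum, the 95% range of the difference in CTTH share is ±1.96 × √(2p(1 − p)/87): ±9 percentage points at p = 0.1 and ±15 at p = 0.5. A 15-point imbalance with D = 1.0 cm shifts the estimate by 0.15 × 1.0 = 0.15 cm. The standard error of the treatment difference is 1.5 × √(2/74) = 0.25 cm, so even this shift lies within ordinary sampling error.

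**Step 4: what a subtype analysis could show.** The interaction has SE = 1.5 × √[(2/74)(1/p + 1/(1 − p))], which is 0.82 at p = 0.1 and 0.49 at p = 0.5. Multiplying by 1.96 + 0.8416, the interaction detectable at 80% power is 2.3 cm and 1.4 cm respectively. Power for a 1.0 cm interaction is 23–53%.

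**The case against.** The strongest reply is that this belongs to the analysis plan. Section 2.10 refers to such a plan, which is not shown, and the covariate list is open-ended. Full covariate lists and subgroup analyses are commonly left to that document. This stands as far as subgroups go: the lack of a stated subtype analysis is no finding. It also means the t-test may not be the final primary analysis, since section 2.10 mentions a mixed model too and does not say which is primary. What remains is that the article does state a t-test for the between-group comparison, and that the covariates it chose to name omit the two its own content points to.

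A second reply is that the pooling is deliberate and explained. The target population is patients sharing one CM pattern, and the analgesic contrast in section 1 concerns other drugs and says nothing about XFZY. This also stands. It supports enrolling both subtypes; it does not bear on whether subtype predicts outcome, which is all that covariate adjustment needs.

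A third is that the article never says an ETTH/CTTH field is recorded. That is correct. Subtype should be derivable from the ICHD-3 diagnosis or from week-0 headache frequency, but this is an inference to be confirmed.

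**Conclusion.** A modest improvement to the analysis, not a flaw in validity. For subtype the gain is about 1–11% of variance if the subtypes differ by 0.5–1.0 cm, up to 25% only if they differ by 1.5 cm with an even split, and nil if they do not differ. Baseline VAS should add to this by an amount the article does not allow one to compute. All of it rests on an assumed CTTH share of 10–50% and a total SD of 1.5.

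A reader might infer more: that pooling two disorders biases the comparison, that ignoring subtype definitely costs precision, or that a planned interaction test would settle whether the treatment works in both. The documents support none of these. Allocation is random within centre, so the pooled difference is a valid estimate for the enrolled mix, and chance imbalance is already covered by its standard error. The precision cost turns on a subtype difference that is not given. An interaction test of this size would miss a 1.0 cm difference about half the time at best (power 53% at an even split).

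**What to change.** Keep randomisation as it is. State in the analysis plan that the primary comparison of VAS change at week 12 is a covariate-adjusted model (ANCOVA, or the linear mixed model already mentioned) with treatment, centre, week-0 VAS and ETTH/CTTH status as fixed covariates. Define subtype once, before unblinding, from the ICHD-3 diagnosis or week-0 headache days. In a linear model the adjusted coefficient estimates the same average difference as the t-test, so the comparison with the 1.7 margin is unchanged. Effects by subtype with 95% confidence intervals may be added, labelled exploratory.

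The cost is a short piece of analysis-plan wording, a check that subtype can be derived from the data collected, and a few degrees of freedom. Nothing changes for patients, visits or allocation. If the unseen plan already specifies this, the sponsor need only confirm it.

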## Figures and Tables

**Figure 1 fig1:**
[figure not shown]
Study flow chart.

**Table 1 tab1:** QBS diagnosis scale.

Symptoms/signs	Yes	No	Score
Pain	9	0	
Irritability/depression	16	0	
Distending pain	2	0	
Scurry pain	6	0	
Chest distress	0.5	0	
Lumps in body	7	0	
Petechia in the tongue	4	0	
Purplish tongue	1	0	
Unsmooth pulse	4	0	
Deep pulse	2	0	
Total score If ≥20 points, diagnosed as QBS			

Notes: pain includes stomachache, abdominal pain, low back pain, dysmenorrhea, breast pain, and limb pain. QBS: *Qi*-stagnation and Blood-stasis pattern.

**Table 2 tab2:** Outcome measures.

Domain	Measure	Time (weeks)
*Primary*		
Mean pain intensity of headache change	10 cm VAS with “none” and “very severe” at either end	0, 1, 2, 4, 8, 12
Secondary		
AUC	Calculated by the sum of the daily headache duration (hours) multiplied by the daily headache intensity in each observed period and, then, divided by the observation period	0, 1, 2, 4, 8, 12
Headache frequency	Defined as a ≥50% reduction by the number of days with a headache or attacks per evaluation period; headache hours for each observed period	0, 1, 2, 4, 8, 12
Headache hours	The total hours in each observed period	0, 1, 2, 4, 8, 12
Rescue medication use	Records the number of participants using the rescue medication and the total dosage per week	0, 1, 2, 4, 8, 12
QBS measurement	Evaluated by a qualified CM physician	0, 1, 2, 4, 8, 12
Quality of life	EQ-5D-5L	0, 4, 12
Global evaluation of medication	A simple verbal scale: very poor, poor, neutral, good, very good	4
Health economic indexes	Registration costs, laboratory tests, drugs (other than the experimental drug), hospital admission, transportation, average monthly income, costs incurred by family caregivers	0, 1, 2, 4

VAS: visual analogue scale, AUC: area-under-the-headache curve. EQ-5D-5L: EuroQol-5-Dimensions-5-Level.

## Data Availability

The datasets used and analyzed in the current study are available from the corresponding author on reasonable request after the study completion. The date and version identifier of the protocol are V1.0/20190920.
